## Overview

### Background and outline

Breast cancer is the most frequent type of cancer for females. The death rate from breast cancer is higher than that from any other cancer for the age group 30-69. Among others, the age group 40-49 has recently been showing a marked increase in the incidence of breast cancer. Therefore, there is an urgent need to countermeasures for reducing the death rate from breast cancer among women in this age group.

Mammography, which is a global standard of breast cancer screening, is low in accuracy when used for breasts with high mammary gland density. High density breasts are often seen at ages less than 50 and more frequent among Japanese women than among Western women. Ultrasonography has high accuracy when used for checking breasts with high mammary gland density. Attempts to use ultrasonography as a means of breast cancer screening have already begun to be made. However, neither the specifications of devices for breast ultrasonography nor its procedure and image reading techniques have yet been standardized. Furthermore, the accuracy and usefulness of ultrasonography as a means of breast cancer screening have not been endorsed.

This study is designed to compare the effect in reducing the death rate from breast cancer between two groups of women, i.e., between women screened with standardized ultrasonography + mammography and women screened with mammography without ultrasonography.

Standardization and spread of  
ultrasonographic breast cancer screening

[figure not shown]

Subjects : Women aged 40-49 (60,000 women/group)  
Comparison : Mammography + Ultrasonography Group vs Mammography Group  
Outcome : Accuracy (sensitivity, specificity), Cumulative incidence of advanced breast cancer

[figure not shown]

Reduction in death rate from breast cancer

Objectives:

Evaluation of the accuracy and usefulness of ultrasonic screening of breast cancer.

Areas covered

Facilities and organization (openly invited for participation) providing breast cancer screening in Japan

Method of intervention

About 120,000 women aged 40-49 are divided into the intervention group (screened with mammography + ultrasonography) and the non-intervention group (screened without ultrasonography).

Endpoints

Primary endpoint: Inter-group comparison of sensitivity, specificity and detection rate.

Secondary endpoint: Inter-group comparison of the cumulative incidence of advanced breast cancer during the follow-up period

Study period

July 2007 through March 2013

Research leader

[name], Professor, Department of Surgical Oncology, Tohoku University Graduate School of Medicine

## 1. Background

Since 1994, the incidence of breast cancer has been higher than that of any other female cancer. Among other, the incidence of this cancer in females aged between 40 and 49 is expected to further rise from now on following changes in the lifestyle of Japanese people [1,2,3]. Premenopausal breast cancer, developing at age 40-49, has been sharply increasing in recent years, and this cancer is related to estrogen, one of the female hormones. It is said that women with lower age of menarche, no history of delivery and delay in menopause are more likely to develop breast cancer because of prolonged exposure to estrogen [3]. However, primary prophylaxis, designed to remove these factors, is not realistic. Under the current trend for less child delivery by individual women, a valid means of preventing death from breast cancer is secondary prophylaxis designed to facilitate early detection of breast cancer, i.e., development, spread, utilization and improvement of a valid method of breast cancer screening.

Breast cancer screening with mammography has been shown in multiple randomized comparative studies in Western countries to be useful in reducing the death rate from breast cancer among women aged over 50, and has been adopted as a global standard. However, the usefulness of this way of screening in reducing the death from breast cancer is lower for women aged 40-49 than for women aged over 50 [4,5,6]. Furthermore, mammography is less accurate for screening of breasts with high mammary gland density [1]. High dense breasts are more often seen in women younger than 50 and are more frequent in Japanese women than in Western women [8]. Furthermore, since the peak age for onset of breast cancer is 40-49 in Japanese women in contrast to the peak age (70-79) in Western women, screening of Japanese women using mammography alone is not expected to be satisfactorily useful [1,2].

Ultrasonography has high accuracy when used for checking breasts with high mammary gland density. Attempts to use ultrasonography as a means of breast cancer screening have already begun to be made. It has been reported that screening with a combination of mammography and ultrasonography has elevated the breast cancer detection rate [9,10,11]. However, neither the specifications of devices for breast ultrasonography nor its procedure and image reading techniques have yet been standardized. Furthermore, the usefulness of ultrasonography as a means of breast cancer screening has not been endorsed.

Nowadays, in both Japan and foreign countries, a prerequisite for performing “cancer screening as a means of countermeasure” under public initiatives is availability of scientific evidence for death rate-reducing effect of the screening [12,13,14]. The Anti-Cancer Basic Act, enforced in April 2007 in Japan, states in Article 18 of Chapter 3

(Basic Policies) that the state and local governments shall promote studies on elucidation of the essential nature of cancer, development of innovative methods for prevention, diagnosis and treatment of cancers, and means for reducing the incidence and death rate of/from cancers and take necessary measures for effective utilization of the outcomes from such studies [15].

In Japan, breast cancer screening was started under the second senile health program in 1987, initially using clinical breast examination. However, since breast cancer screening with clinical breast examination failed to reduce the death rate [16,17], the Guideline on Cancer Screening was partially amended in 2000 to adopt a combination of clinical breast examination and mammography for women aged over 50 (Notification No. 65, Health and Welfare Bureau for the Elderly, MHLW, March 31, 2000). Breast cancer screening for women aged 40-49 previously used clinical breast examination. In 2004, the state partially amended the Guideline on Cancer Prevention-Focusing Health Education and Cancer Screening (Notification No. 0427001, Division of the Health for the Elderly, the Health and Welfare Bureau for the Elderly, MHLW, April 27, 2004) to adopt mammography as a means of screening, as a rule. However, according to the results of randomized comparative studies in Western countries, the death rate-reducing effect of mammography is lower for women aged 40-49 than for women aged over 50 [4,5,6]. Under such circumstances, the interim report from the Cancer Screening Committee, organized under MHLW, made the following two arguments (March 2004) [18].

1. Although ultrasonography is useful in clinical management of breast cancer, no evidence is available for its effect in reducing the death rate from breast cancer.
2. It is desirable from now on to evaluate the usefulness of ultrasonic breast cancer screening and to facilitate standardization of the devices, imaging techniques and image reading techniques related to the screening and to establish a firm diagnostic base for this kind of screening. It is advisable to consider utilization of ultrasonography for screening of individuals with high density breasts whose lesions are difficult to depict by mammography.

Following that report, the report from the research in fiscal 2005 (Chief Researcher: [name]), carried out within the framework of Research on Strategic Outcomes (Ministry of Health, Labour and Welfare Scientific Research Program), proposed to carry out a randomized comparative study on ultrasonic breast cancer screening [19].

In response to the proposal made by the strategic outcome research group

mentioned above, we have devised a protocol for a study designed to compare the usefulness of ultrasonic breast cancer screening with conventional methods of screening after achieving standardization of the devices, imaging techniques and image evaluation techniques related to ultrasonic screening.

## 2. Objectives

This study is designed to compare the accuracy and usefulness of breast cancer screening of women aged 40-49 between two groups (a group screened with a combination of mammography and ultrasonography and a group screened with mammography without combined with ultrasonography) after standardization of ultrasonic breast cancer screening procedure.

The primary endpoint of this study is inter-group comparison of the sensitivity, specificity and detection rate. The secondary endpoint is inter-group comparison of the cumulative incidence of advanced\* breast cancer during the follow-up period. (\*According to the General Rules for Surgical and Pathological Studies on Breast Cancer prepared by the Japanese Breast Cancer Society, breast cancers having metastasized to lymph nodes or distant organs are defined as “advanced breast cancers.”)

The most important indicator of the usefulness of cancer screening is the death rate from a given type of cancer in the population studied. However, in view of the natural history of breast cancer, the four-year period of strategic research is too short to explore a significant inter-group difference in this indicator. Therefore, a system will be established to allow long-term follow-up of the survival/death of the subjects of this study in both groups after completion of this strategic research.

## 3. Study design

This study is designed to compare the accuracy and usefulness of breast cancer screening of women aged 40-49 between two groups, i.e., the intervention group screened with a combination of mammography and ultrasonography and the non-intervention group screened with mammography. To this end, the below shown two groups are incorporated into this study, with individuals or clusters serving as units.

- (1) Ultrasonography combined group (mammography + ultrasonography or mammography + clinical breast examination + ultrasonography)
- (2) Ultrasonography uncombined group (mammography alone, or mammography + clinical breast examination)

The targeted number of subjects is 60,000 for each group (120,000 subjects in

total). Of these subjects, 50,000 subjects from each group will receive two sessions of breast cancer screening at an interval of 2 years.

The targeted number of subjects was set on the basis of the forecast as to the capability of elevating the sensitivity (the primary endpoint) by the use of ultrasonography in combination with conventional mammography.

In analysis of the intermediate period cancer (cancer detected before the next session of screening after the latest session of screening yielding a judgment of “abnormality-free”), using the data from the Miyagi Prefecture Regional Cancer Registry, the sensitivity of breast cancer screening with a combination of mammography and clinical breast examination was higher than that of screening with clinical breast examination alone in each age group, but the sensitivity of this combined screening was lower in the age group 40-49 (71.4%) than in any other age group (age group 50-59: 85.8%, age group 60-69: 87.2%) [7]. Of the 20,587 subjects aged 40-49 in that study, 63 had breast cancer during the two-year period after the screening, including 45 cases detected during the screening and 18 cases detected during the intermediate period (sensitivity  $45/63=71.4\%$ ). Assumed that the addition of ultrasonography to the screening will increase the number of breast cancers detected during screening and that the number of intermediate cancer cases will be halved (from 18 to 9 cases), the sensitivity of the ultrasonography-combined screening will be 86% ( $54/63$ ). So that this increase in sensitivity can be detected as a significant difference at a significance level of 5% (both-sided) and with a detective power of 80%, the number of breast cancer cases required will be 130. The minimum necessary number of subjects screened is thus estimated to be 42,500 for each group. Therefore, if 50,000 subjects can be enrolled to each group, a valid statistical analysis of the increase in sensitivity following the addition of ultrasonography will be possible.

Then, we analyzed the number of subjects needed for valid analysis of the secondary endpoint (decrease in the cumulative incidence of advanced breast cancer). In the above-mentioned mammography screening group, advanced breast cancer was detected in 12 subjects (27.7%) during the screening and 6 subjects (30.6%) during the intermediate period, with the incidence of advanced breast cancer being 87/100,000 population ( $18/20587$ ). Assumed that the percentage of advanced breast cancer is the same also in the ultrasonography-combined screening group, the incidence of advanced cancer group in the ultrasonography-combined screening group will be 74/100,000 population ( $15/20587$ ). So that this difference can be detected as a statistically significant difference at a significance level of 5% (both-sided) and with a detective power of 80%, the number of necessary subjects screened is 760,000 for each group.

Assumed that the survival rate is 96%, 85%, 92% and 50% for patients with early breast cancer detected during screening, advanced breast cancer detected during screening, early breast cancer detected during the intermediate period and advanced breast cancer detected during the intermediate period, respectively, the death rate from breast cancer will be 34/100,000 population for the mammography group and 26/100,000 population for the ultrasonography-combined group. To detect this difference as a statistically significant difference at a significance level of 5% (both-sided) at a detective power of 80%, 760,000 subjects are at least needed for each group. Taken together, these results indicate that a study whose endpoint is the incidence of advanced breast cancer or the death rate from breast cancer after a single session of screening is of little statistical value.

Meanwhile, assumed that the percentage of advanced cancers among all intermediate period cancer cases can be reduced to 10%, the death rate from breast cancer will be 34/100,000 population in the mammography group and 22/100,000 population in the ultrasonography-combined group (36% smaller in the latter group), indicating that the final outcome of this study (reducing the death rate from breast cancer by 30%), a target proposed by the [name] Group, can be achieved. Assumed that screening is continued for 10 years at intervals of 2 years, the cumulative death rate from breast cancer will be 170/100,000 population and 110/100,000 population for the two groups, respectively. To detect this difference as a statistically significant difference at a significance level of 5% (both-sided) and with a detective power of 80%, 55,000 subjects are at least needed for each group. Therefore, if screening can be continued for 10 years, a statistically valid analysis of a decrease in death rate from breast cancer following the addition of ultrasonography will be possible by enrollment of at least 60,000 subjects to each group.

Study designs available for obtaining scientific evidence include individual randomized study, cluster randomized study, cluster non-randomized comparison, etc. From the viewpoint of conducting a high-quality study, validity seems to be highest for the individual randomized study design by which individual subjects, having given informed consent, are assigned at random to one of the ultrasonography-combined group and the ultrasonography-uncombined group. A study design with the second highest validity will be cluster randomized study design by which assignment to the ultrasonography-combined group or the ultrasonography-uncombined group is made at random in units of local community (town or village) or workshop (place of work). If randomized assignment is difficult, cluster non-randomized comparison (a study design by which comparison with the non-intervention group is made, although assignment is

not made) has to be selected.

Another possible study design will be an independent study in which only one type of screening is made (either ultrasonography-combined screening or ultrasonography-uncombined screening), but this study cannot be viewed as a comparative study. For the present study, it is desirable to adopt a study design capable of providing scientific evidence as far as possible. For this reason, participation in this study will be accepted with emphasis laid on the organizations or facilities which intend to perform the study by means of individual randomized comparison, cluster randomized comparison or non-randomized comparison (greatest emphasis laid on the first study design and progressively less emphasis on the next two designs).

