In the above-mentioned mammography group, 12 subjects (27.7%) and 6 subjects (30.6%) had screen-detected breast cancer and advanced breast cancer as interval cancer respectively, and the cumulative incidence of advanced breast cancer was 87 per 100000 (18/20587). For this ratio of advanced breast cancer, assuming that the number of subjects with advanced breast cancer as interval cancer would be also decreased by half (decrease from 6 to 3 subjects) in the ultrasonography combined group, the cumulative incidence of advanced breast cancer in the ultrasonography combined group would be 74 per 100000 (15/20587). A total of 760000 subjects per group would be necessary for demonstrating this with a two-sided significance level of 5% at a power of 80%.

In addition, when the survival rates of screen-detected early breast cancer, screen-detected advanced breast cancer, early interval breast cancer, and advanced interval breast cancer would be 96%, 85%, 92% and 50%, respectively, the cumulative mortality of breast cancer in the mammography group and ultrasonography combined group would be 34 per 100000 and 26 per 100000, respectively. A total of 760000 subjects per group would be necessary for demonstrating these with a two-sided significance level of 5% at a power of 80%. Therefore, a study using the cumulative incidence of advanced breast cancer or the mortality of breast cancer with provision of one screening session as the endpoints is substantially meaningless in terms of statistics.

In contrast, of interval cancers, if the ratio of advanced cancer could be decreased up to 10%, the cumulative mortality of breast cancer in the mammography group and ultrasonography combined group would be 34 per 100000 and 22 per 100000, respectively (reduction in the mortality by 36%). Thus, the final outcome of this study shown by [name] Group, "a decrease in the mortality of breast cancer by 30%" could be achieved. If screening would be continued once every two years for 10 years, the cumulative mortality of breast cancer in each group would be 170 per 100000 and 110 per 100000, respectively. A total of 55000 screened subjects per group would be necessary for demonstrating these with a two-sided significance level of 5% at a power of 80%.

161 3. Planned Period of the Study

162 3.1 Schedule of the first and second screening and the number of subjects to be enrolled

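### The advanced-cancer and mortality figures rest on an unstated assumption that all nine extra screen-detected cancers are early, and 55,000 per group does not give 80% power at the printed 10-year rates

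*Combined protocol and SAP*

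**What the plan says.** Protocol section 3 starts from a regional registry series: "Of the 20,587 subjects aged 40-49 in that study, 63 had breast cancer during the two-year period after the screening". Of these 63, screening found 45 and the other 18 were interval cancers. With ultrasonography, interval cancers are assumed to halve from 18 to 9, so the split becomes 54 screen-detected and 9 interval.

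In the mammography series, 12 screen-detected cancers (printed as 27.7%) and 6 interval cancers (printed as 30.6%) were advanced, 87 per 100,000 in all. For the ultrasonography group the protocol states: "Assumed that the percentage of advanced breast cancer is the same also in the ultrasonography-combined screening group". It then prints 74 per 100,000 (15/20587) and a need for 760,000 per group. With four assumed survival rates it prints deaths of 34 versus 26 per 100,000.

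The next paragraph of section 3 lowers the advanced share of interval cancers to 10%. It prints 34 versus 22 deaths per 100,000, described as "36% smaller in the latter group", and says the 30% reduction target can be met. Over ten years of two-yearly screening this becomes 170 versus 110 per 100,000, and "at a significance level of 5% (both-sided) and with a detective power of 80%, 55,000 subjects are at least needed for each group". It concludes that 60,000 per group would allow a valid mortality analysis.

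SAP 2.5 (secondary endpoint) carries the same figures. There the assumption is that advanced interval cancers are halved: "decrease from 6 to 3 subjects". It says nothing about the stage of the additional screen-detected cancers.

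**The concern.** Nine cancers move from interval to screen-detected. If the advanced share is unchanged in each mode, some of those nine are advanced, and the total number of advanced cancers hardly moves. A fall from 18 to 15 requires that none of them is. That is a strong down-staging assumption. It produces the whole printed difference in advanced incidence and part of the printed difference in deaths, and neither document puts it into words.

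Advanced-cancer incidence is the declared secondary endpoint. The protocol calls the death rate the most important indicator of usefulness and plans long-term follow-up for it. Anyone reading a null result on either outcome will go back to these figures to judge what the trial could have detected.

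**Working it through.** **Inputs.** Protocol section 3: 20,587 women; 45 screen-detected and 18 interval cancers, becoming 54 and 9; advanced 12 and 6; survival 96%, 85%, 92% and 50% for early screen-detected, advanced screen-detected, early interval and advanced interval cancers. The printed 27.7% and 30.6% do not equal 12/45 = 26.7% and 6/18 = 33.3%, so results are given on both bases.

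**Advanced incidence.**
- Printed 74: 45 × 0.277 + 9 × 0.306 = 15.2 cases, or 73.9 per 100,000. From counts, 12 + 3 = 15, or 72.9. The screen-detected term still uses 45, so the share falls from 12/45 (26.7%) to 12/54 (22.2%).
- Share held in both modes: 54 × 0.277 + 9 × 0.306 = 17.7 cases, or 86.0 per 100,000. From counts, 14.4 + 3 = 17.4, or 84.5.

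**Deaths.** Rate = (0.04 × early screen + 0.15 × advanced screen + 0.08 × early interval + 0.50 × advanced interval) / 20,587.

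| Per 100,000 | Printed | Extra nine all early (counts; percentages) | Screen-detected share held (counts; percentages) |
|---|---|---|---|
| Mammography | 34 | 34.4; 33.6 | same |
| Ultrasonography | 26 | 26.5; 26.3 | 27.8; 27.6 |
| Ultrasonography, 10% of interval cancers advanced | 22 | 22.2; 22.5 | 23.5; 23.8 |

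Example from counts, 10% scenario, share held: 39.6 × 0.04 + 14.4 × 0.15 + 8.1 × 0.08 + 0.9 × 0.50 = 4.842 deaths, and 4.842/20,587 = 23.5 per 100,000. Only the all-early column is consistent with the printed 26 and 22.

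**Sample size formula.** n = [1.96√(2p̄(1−p̄)) + 0.84√(p₁(1−p₁) + p₂(1−p₂))]² / (p₁−p₂)², two-sided 5%, 80% power. With continuity correction it reproduces both figures of 760,000: 87 versus 74 gives 762,438, and 34 versus 26 gives 760,406.

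**10-year size at the printed rates.** With p₁ = 0.00170 and p₂ = 0.00110, the numerator is (0.1036 + 0.0445)² = 0.02195. Divided by 0.0006² this is about 60,960. With continuity correction it is about 64,250; one-sided it is 48,019 (51,298 corrected). None is 55,000. Two-sided power at 170 versus 110 is 75.8% at 55,000, 79.4% at 60,000, and 62.1% at the 40,000 per group in the SAP 3.1 schedule (5,000 + 15,000 + 15,000 + 5,000).

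**Relative reduction.** 1 − 22/34 = 35.3%. The unrounded all-early chain gives 35.3% from counts and 33.1% from percentages.

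**Effect of holding the share.**
- Advanced incidence: 87.4 versus 84.5 needs about 16 million per group (counts); 87.3 versus 86.0 needs about 85 million (percentages).
- 10% scenario, ten years (five rounds), no continuity correction:

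| | Counts | Percentages |
|---|---|---|
| Rates per 100,000, share held | 172.0 vs 117.6 | 168.2 vs 119.1 |
| Reduction | 31.6% | 29.2% |
| n per group, share held | 76,800 | 93,400 |
| n per group, all early | 60,100 | 70,800 |
| Power at 60,000, share held | 70% | 61% |

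**The case against.** The SAP's 6-to-3 wording and the printed 15/20587 suggest that the figures, not the sentence, were intended. The protocol sentence can then be read as keeping the advanced share unchanged among interval cancers only (6/18 to 3/9). This stands as a reason to correct the sentence first. It does not supply the missing statement that all the extra screen-detected cancers are early.

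A reader might infer that the treatment effect is simply overstated. The documents do not support that: it is overstated only relative to the written sentence, and nothing in them settles which stage mix was meant. The 10-year paragraph also changes only the interval share and is silent on the screen-detected share. Holding the latter there is a sensitivity case, not the plan's stated assumption.

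A reader might also put the whole gap between 55,000 and 77,000 to 93,000 down to stage mix. It is not so: 55,000 already falls short at the printed rates, and stage mix moves 60,100 to 76,800 (counts) or 70,800 to 93,400 (percentages). Nor is the 30% claim unconditional as printed. It depends on the 10% assumption, and the 10-year conclusion depends on screening continuing for ten years.

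Rounding explains part of the rest. An unrounded 34.4 against a rounded 22 gives 36%. The matching 172 versus 110 needs about 57,500, or about 55,700 by Schoenfeld's formula. That mixes bases and is not what the documents print.

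Finally, the target number was set on sensitivity, and section 3 already calls single-session advanced-cancer and mortality endpoints of little statistical value. Both points are correct and limit the consequence.

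**Conclusion.** The point holds as a mismatch between stated assumption and printed figures, plus a separate sample-size error. The printed 74, 26 and 22 per 100,000 need an assumption that neither document states. Under equal shares in both modes, the single-round difference in advanced incidence nearly vanishes (84.5 to 86.0 against about 87). In the 10-year scenario the reduction is 29% to 32%, on either side of the 30% target. The ranges reflect the two inconsistent bases in the protocol, counts and percentages.

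Independently of stage mix, 80% power at 170 versus 110 needs about 61,000 per group (64,000 with continuity correction). The planned 60,000 comes close at 79%; the 40,000 scheduled in SAP 3.1 gives 62%. These figures assume a simple two-proportion comparison with no allowance for dropout or clustering. The primary-endpoint size of 42,500, the analysis sets and the analysis methods are unaffected.

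**What to change.** In protocol section 3 and SAP 2.5, in the same words:
- State the assumption used: advanced screen-detected cancers unchanged at 12, all additional screen-detected cancers early.
- Restate 55,000 as about 61,000 (or 64,000 if the continuity correction behind the 760,000 figures is kept) and 36% as about 35%.
- Give the 10-year power at the planned number: 79% at 60,000 and 62% at 40,000 for 170 versus 110.
- Add the equal-stage-mix result as a sensitivity case: 29% to 32% reduction, 77,000 to 93,000 per group.
- Make the statement on the 30% target conditional on the down-staging assumption as well as on the 10% assumption.

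The cost is wording and recalculated figures in two sections. No additional women, data or analyses are needed.

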## 2.5 Sample size

### Primary endpoints:

The primary endpoints are defined as differences in sensitivity/ specificity and a detection rate of the first breast cancer screening between the intervention group and non-intervention group as previously mentioned. The sample size was calculated based on a previous study comparing sensitivity between screening with CBE alone and mammography in combination with CBE.

In this study that was used for understanding interval cancer (cancer identified in screened individuals without abnormality during a period between the screening and the next screening) in population-based cancer registry data in Miyagi Prefecture, the sensitivity of breast cancer screening using mammography in combination with CBE was superior to that of CBE alone in all age groups. However, the sensitivity was 71.4% for the age of 40 to 49 years, 85.8% for the age of 50 to 59 years, and 87.2% for the age of 60 to 69 years; thus, it was lowest for the 40's. Of 20,587 subjects aged 40 to 49 years, breast cancer occurred in 63 subjects during two years after screening including screen-detected breast cancer. Of these, screen-detected breast cancer was in 45 subjects, and interval cancer was in 18 subjects (sensitivity:  $45/63 = 71.4\%$ ).

Furthermore, assuming that a combination with ultrasonography would increase the number of subjects with screen-detected cancer and that the incidence of interval cancer would be decreased by half (decrease from 18 to 9

subjects), sensitivity in the ultrasonography combined group would be 86% (54/63). A total of 130 subjects with breast cancer would be necessary for demonstrating this increase in sensitivity with a two-sided significance level of 5% at a power of 80%. When it was converted to the number of subjects undergoing screening, a sample size of 42,500 subjects per group was estimated.

Secondary endpoint:

The secondary endpoint is defined as difference in the cumulative incidence rate of advanced breast cancer during the follow-up period between the intervention and non-intervention groups as previously mentioned. As with the primary endpoints, the sample size was calculated based on the previous study comparing sensitivity between screening with CBE alone and mammography in combination with CBE.

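### The 10-year mortality projection applies the age 40-49 sensitivity to all five rounds although women pass 50, so 55,000-60,000 per group does not give the stated 80% power

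*Combined protocol and SAP*

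**What the plan says.** Protocol section 3 models one round from a registry study of women aged 40-49 and, with ultrasonography reducing the advanced share of interval cancers to 10%, concludes that "the death rate from breast cancer will be 34/100,000 population in the mammography group and 22/100,000 population in the ultrasonography-combined group", which it calls a 36% reduction. It then projects this over ten years: "Assumed that screening is continued for 10 years at intervals of 2 years, the cumulative death rate from breast cancer will be 170/100,000 population" in the mammography group, against 110/100,000 in the ultrasonography-combined group. From this it derives the requirement: "significance level of 5% (both-sided) and with a detective power of 80%, 55,000 subjects are at least needed for each group". It goes on to say that enrolling at least 60,000 per group makes a valid mortality analysis possible if screening can continue for 10 years.

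SAP 2.5 repeats the projection ("If screening would be continued once every two years for 10 years") with the same 170, 110, 55,000 and 36%.

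Both documents also report control-arm sensitivity by age. The protocol gives 71.4% at 40-49 and, for older women, "age group 50-59: 85.8%, age group 60-69: 87.2"%. SAP 2.5 gives "71.4% for the age of 40 to 49 years, 85.8% for the age of 50 to 59 years". Eligibility is age 40-49 at enrolment (protocol 4.1).

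**The concern.** Multiplying one round by five treats every woman as if she stayed 40-49 for ten years. Many will be 50 or over in the later rounds. There the control sensitivity in the plan's own source (85.8%) already equals the level assumed for ultrasonography-combined screening at 40-49 (86%). Fewer interval cancers are left to prevent, so the benefit per round shrinks.

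At stake is the claim that a 10-year programme with 60,000 per group supports a valid mortality analysis. This is the only calculation in the documents that arrives at 60,000; the sensitivity calculation stops at 42,500, rounded up to 50,000. Mortality is described as the most important indicator (protocol 2 and 11.2) and is to be analysed and reported from long-term follow-up (protocol 19). If the power is overstated, a later null mortality result could be misread as evidence of no benefit.

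**Working it through.** **Inputs (protocol section 3, repeated in SAP 2.5).** 20,587 women aged 40-49; 63 cancers in two years, 45 screen-detected (12 advanced) and 18 interval (6 advanced). With ultrasonography, interval cancers are halved and 10% of them are advanced. Survival: 96% early screen-detected, 85% advanced screen-detected, 92% early interval, 50% advanced interval. Two-sided 5%, 80% power, five rounds.

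**1. Reproduce the one-round rates.** Deaths = 0.04 × early screen + 0.15 × advanced screen + 0.08 × early interval + 0.50 × advanced interval. The 9 extra screen-detected cancers are taken as early.
- Control: 0.04×33 + 0.15×12 + 0.08×12 + 0.50×6 = 7.08, or 34.4 per 100,000 (stated 34).
- Combined: 0.04×42 + 0.15×12 + 0.08×8.1 + 0.50×0.9 = 4.58, or 22.2 per 100,000 (stated 22).

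The model is recovered. Then 5 × 34 = 170 and 5 × 22 = 110 exactly. The reduction from 34 to 22 is 35.3%; the plan prints 36%.

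**2. Check the stated N on the plan's own rates.** n = [z₀.₉₇₅√(2p̄(1−p̄)) + z₀.₈₀√(p₁(1−p₁) + p₂(1−p₂))]² / (p₁−p₂)², with p₁ = 0.00170 and p₂ = 0.00110.
- n = 60,961 per group, or 64,251 with continuity correction. The plan's 760,000 for 34 v 26 does reproduce with that correction (760,406); the 55,000 reproduces with neither form.
- Power is 75.8% at 55,000 and 79.4% at 60,000.

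**3. Share of rounds at 50 or over.** The documents give no age distribution. With even entry ages 40-49 and rounds at years 0, 2, 4, 6 and 8, the shares are 0, 20, 40, 60 and 80%, mean 40%. The bounds are 16% if all enter at 40-44 and 64% if all enter at 45-49.

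**4. One round at 50-59.** Only sensitivity changes, to 85.8%. The 63 cancers, advanced shares, survival and ultrasonography effect are carried over.
- Interval cancers: 63 × 0.142 = 8.95 (2.98 advanced). Screen-detected: 54.05 (14.41 advanced).
- Control: 0.04×39.64 + 0.15×14.41 + 0.08×5.96 + 0.50×2.98 = 5.72, or 27.8 per 100,000.
- Combined (4.47 interval, 10% advanced): 0.04×44.11 + 0.15×14.41 + 0.08×4.03 + 0.50×0.447 = 4.47, or 21.7 per 100,000.

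The difference per round falls from 12.2 to 6.0 per 100,000.

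**5. Five rounds, 60/40 mix.**
- Control: 5 × (0.6×34.39 + 0.4×27.77) = 158.7.
- Combined: 5 × (0.6×22.24 + 0.4×21.72) = 110.2.
- Reduction: 1 − 110.2/158.7 = 30.6%.
- The formula in step 2 gives about 89,400 per group. Power is 59% at 55,000 and 63% at 60,000.

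**6. Range (the rest as in step 5).**

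| Assumption for 50-59 | N per group | Power at 60,000 |
|---|---|---|
| 16% of rounds at 50 or over | 69,600 | 74% |
| 64% of rounds at 50 or over | 120,200 | 51% |
| Incidence 0.7 times that at 40-49 | 92,900 | 61% |
| Incidence 2 times | 78,400 | 69% |
| Ultrasonography removes every interval cancer | 76,600 | 70% |
| Incidence 1.5 times, half of control interval cancers advanced | 63,200 | 78% |
| Incidence 2 times, half of control interval cancers advanced | 56,200 | 82.5% |

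Taken singly, 80% at 60,000 needs incidence about 4.25 times that at 40-49, or an advanced share of control interval cancers about double (33% to roughly 67%).

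**The case against.** The strongest reply has four parts.

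- **Most 50-59 inputs are assumed.** Sensitivity is the only one that the documents give by age. Incidence, advanced share, survival and the ultrasonography effect are carried over from 40-49, and the 40% is an assumption. This stands, and it is why a range is shown. A joint rise in incidence and advanced share could bring power back to about 80%. The documents do not point that way: protocol section 1 puts the peak age of onset at 40-49 in Japanese women. The 85.8% is for mammography plus clinical breast examination, but so is the plan's 71.4%.
- **Age does not explain the whole shortfall.** This also stands. At 55,000 the plan's own rates give 76%, so the age mix takes power from 76% to 59%, not from 80%.
- **The multiplication is correct.** True: 5 × 34 and 5 × 22 are right. The fault is the assumption that all five rounds are alike.
- **The consequence is limited.** Mortality is neither the primary nor the secondary endpoint, the protocol says the target number was set on sensitivity, and the statement is conditional on ten years of screening, while the schedules show at most two rounds per woman. This lowers the severity. It does not rescue a power claim stated for a specific N.

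A reader might also infer that, because the survival rates carry no time horizon, deaths after year 10 are being counted as 10-year deaths. The documents do not support that. They describe ten years of screening and a cumulative death rate, set no mortality cut-off at year 10, and foresee long-term follow-up after the study without an end date.

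**Conclusion.** The concern holds. The 170 v 110 projection ignores ageing past 50 despite age-specific sensitivity in the same section, and the 80% power claim at 55,000-60,000 is not supported. Without any age correction, 170 v 110 needs about 61,000, so 60,000 is close and 55,000 is not. With the correction, under even entry ages and 40-49 values for everything but sensitivity, N is about 89,400 and power at 60,000 is 63%. It stays between 74% and 51% for any share of later-age rounds from 16% to 64%.

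Two further inferences go too far. The 30% mortality target is not shown to be missed: the base case still gives 30.6%, and only the margin over the target shrinks. Nor does the point touch the trial's primary analysis, because the 42,500 per group for sensitivity does not depend on this projection. Severity is low to moderate.

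**What to change.** In protocol section 3 and SAP 2.5:

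- Recompute the cumulative rates round by round, with control sensitivity 71.4% below age 50 and 85.8% from age 50.
- State the assumed entry-age distribution and the incidence, advanced shares, survival and ultrasonography effect used at 50-59, with a range for each that is not known.
- Replace the 55,000/60,000 power statement and the 36% with the resulting N, the power at the planned number and the reduction. Name the planned number: the protocol targets 60,000 per group, while the SAP 3.1 table totals 80,000, or 40,000 per group, where the base case above gives about 47% power.

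The cost is a few restated sentences in two places and figures less favourable to the mortality aim. No enrolment, endpoint or analysis changes.
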